# 7. TRIAL MATERIALS

1. Hyflux factory bottled ELO drinking water– 1.5 litre oxygen-enriched water
2. Hyflux factory bottled placebo drinking water – 1.5 litres

### 7.1 Trial Product (s)

Trial products include the following:

- ELO water for drinking is oxygen enriched water that comes in a 1.5 litre format
- Placebo drinking water in a 1.5 litre format
- Both bottles look similar and are non-identifiable

### 7.2 Storage and Products Accountability

- The ELO water and placebo drinking water should be stored at room temperature in a cool place away from direct sunlight.

- These study water will be stored at a third party commercial logistics vendor facility and delivered to the patients at regular intervals by the logistics vendor upon the request of the CGH study team.

- An outline of the water delivery process is attached in appendix 1

# 8. TREATMENT

### 8.1. Rationale for Selection of Dose

- ELO water for drinking – 1.5 litres a day in divided servings
- Placebo drinking water – 1.5 litres a day in divided servings
- Patients are advised to consume other forms of beverages or water in addition to the ‘1.5 litre study water’ to make up the recommended 2-3 litre per day for adults.
- The 1.5 litres of study water fulfils 50 – 75% of an adult person’s recommended daily intake of water and is a reasonable amount to ask the patient to drink

### 8.2. Study Product Formulations

- ELO water for drinking in 1.5 litre bottle.
- Placebo drinking water in 1.5 litre bottle.

### 8.3. Study Product Administration

Routes of administration of ELO regime:

1. Oral – drinking 1.5 litres of ELO or Placebo drinking water per day in divided servings in non-metallic vessels. No heating or boiling or microwaving of the ELO water.

### 8.4. Specific Restrictions / Requirements

- Patients advised to comply with their existing prescribed medications

- Patients are advised not to have changes in their diet, physical activity or medications during the 24 week study period

- Patients are advised not to add on any new traditional medications or health supplements during the 24 week study period

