Cell processes occur in a ‘watery’ environment because 70 percent of cells is made of water. Within the living cells, water is used as a carrier of nutrients, electrolytes and oxygen for cell processes such as energy production, protein production and waste management.

Dehydration is a feature in poorly controlled diabetes and can aggravate hyperglycemia^8^ (high blood glucose) in diabetes patients. Chronic dehydration has been implicated as a factor in development of renal disorders including diabetic nephropathy^8^.A review published in the American Journal of Nephrology found that reducing vasopressin secretion, increasing water intake may have a beneficial effect on renal function in patients with all forms of chronic kidney disease (CKD) and may also benefit those at risk ofCKD^10^.The effects of good hydration on renal function of Type 2 diabetes patients should be explored as a simple lifestyle measure that could help ameliorate diabetic nephropathy.

*ELO water – what is it?*

ELO water is a pure drinking water that is enriched with molecular oxygen in a stable form. The ELO water looks and tastes like good quality drinking water without unusual taste or colour. It has passed the AVA standards for drinking water in terms of purity and mineral content and has been on sale commercially in Singapore since November 2015.

Oxygen naturally has low water solubility and has a tendency to immediately escape back into the air from solution. A special proprietary technology, the result of joint technology efforts by Hyflux Ltd and Kagun Europe Zrt Hungary, is able to produce ELO Water with a stable oxygen-enrichment. The oxygen content of ELO water is stable and is between 15 to 19 ppm, much higher than oxygen content in tap water (3-7 ppm)

A study by Ugolev has demonstrated that the mammalian gut lining is capable of oxygen absorption when his study demonstrated that oxygen saturated saline had 50-80% of the dissolved oxygen content absorbed when it was passed through 15 cm of rat gut^10^. Providing both hydration and oxygen, ELO water is an interesting type of water which potentially presents another platform to deliver oxygen and hydration which should be explored.

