## b. Rationale for Doses Selected

It is suggested that 1.5 litres (1 bottle) of ELO water is to be consumed every day for a period of 24 weeks. Other forms of water must be used to supplement this in order to achieve the 2-3 litre total daily requirement of water in an adult.

24 weeks of daily ELO water consumption is a long enough period to ascertain changes in HbA1c.

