## b. End Points – Safety

Safety measures:

- Sponsor to deliver bottled water to patient’s home regularly, to avoid any danger to them if they carry heavy loads of water home.
- Hyflux is a public listed water company in Singapore with high quality standards for water products and ELO Water Pte Ltd is a Hyflux Group company. The ELO water has been approved by AVA Singapore for sale in Singapore since November 2015.

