### 3.4. Exclusion Criteria

1. Type 1 diabetes patients
2. Pregnant or lactating women
3. Comorbid conditions requiring fluid intake restriction
4. Patients who are unable to drink water due to inability to swallow or gastrointestinal conditions e.g. stroke or neurological disorders with inability to swallow fluids safely, bedridden patients with high risk of aspiration pneumonia, patients with oesophageal strictures, radical stomach resections or other conditions that makes drinking water unsafe

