###### Table 2: Study arms

| **Treatment arm** | **ELO water** | **Placebo drinking water** |
| --- | --- | --- |
| Drinking 1.5 Litre water daily | ELO bottled water | Normal bottled drinking water |
| Diabetes treatment | Patient’s existing medications | Patient’s existing medications |

A total of 150 Type 2 diabetes mellitus patients who are eligible for the study will be enrolled into this 24 week study.

1. Each patient will be allocated a subject number for the study.
2. Once consented, patients who are recruited will be stratified according to their gender and will be randomised to the either of the 2 treatment arms (see table 2) in the ratio of 1:1.
3. Baseline blood tests (see table 3) will be done at a CGH clinic or CTRU.
4. Patients in both treatment arms will be issued water for drinking that is delivered to their home regularly (Bottled ELO water 1.5 litres or placebo bottled drinking water 1.5 litres) in non-identifying bottles that do not reveal to the patients as to which type of water they are consuming.
5. Study team member will remind patients regularly (via phone call or text message) to drink the study issued water, in order to archive the compliance.
6. Patients are instructed to consume 1.5 litres in divided servings per day. No metal containers or utensils to be in contact with the ELO water. The water cannot be heated or microwaved and should not be mixed with other beverages and consumed.
7. Patients are advised to drink other fluids or water in addition to the 1.5 litres of the bottled water to fulfil their daily water requirements of about 2-3 litres per day.
8. Patients are advised to strictly continue taking their prescribed existing medications and attend scheduled medical appointments throughout the study period.
9. No changes to be made in their diet, physical activity or medications during the study period.
10. Blood tests are performed at week 0, 6,12, and 24 (see table 3)
11. Patients are instructed to keep a water diary

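### Commercial ELO or other oxygen-enriched water is not explicitly barred, screened for or recorded in either arm, so control-arm use could dilute the oxygen contrast

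*Protocol*

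**What the plan says.** **Availability.** Section 1 (ELO water – what is it?) says the test product "has been on sale commercially in Singapore since November 2015". Section 2.4b repeats that it is approved for sale there. The trial runs at a single centre in that market, under a protocol dated August 2016.

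**Other fluids.** Section 5, item 7 applies to both arms: "Patients are advised to drink other fluids or water in addition to the 1.5 litres of the bottled water", to reach about 2-3 litres per day. Section 8.1 says much the same: "Patients are advised to consume other forms of beverages or water in addition to the" study water. Section 1.1b, which describes the ELO dose, says: "Other forms of water must be used to supplement this in order to achieve the 2-3 litre total daily requirement of water in an adult".

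**Restrictions.** Section 8.4 asks patients to keep to their existing medications and adds two further items: "Patients are advised not to have changes in their diet, physical activity or medications during the 24 week study period" and "Patients are advised not to add on any new traditional medications or health supplements during the 24 week study period". Section 5, item 9 repeats the advice on diet, activity and medications.

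**Eligibility.** The only fluid-related exclusions in Section 3.4 are medical: "Comorbid conditions requiring fluid intake restriction" and inability to drink safely. Current use of oxygen-enriched water is not mentioned.

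**Recording.** Under Table 1, footnote a, each review covers the water diary, adverse effects, and changes in medications, diet and physical activities. Section 8.6 documents medications. No stated item asks about oxygen-enriched water from outside the trial.

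**The concern.** Section 1.1d gives the placebo-water arm one purpose: to separate the effect of the higher oxygen content from the effect of hydration. Oxygen content is therefore the only intended difference between the arms. The protocol controls the 1.5 L it delivers. It says nothing explicit about whether the remaining daily fluid may be the same product bought from a shop.

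If some controls drink it, their outcomes move towards those of the ELO arm. The estimated difference shrinks, and a null result becomes harder to interpret.

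The analysis plan could not repair this later. The per-protocol analysis and the compliance adjustment in Section 11.2 rest on the water diary, whose stated purpose is compliance with the study water. An exposure that was never asked about cannot be recovered at analysis. That makes it a matter of trial conduct, which the protocol has to settle.

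**Working it through.** **1. Coverage of each route, from the text**

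| Route to exposure | Nearest text | Does it clearly cover the route? |
|---|---|---|
| Patient starts buying ELO water during the trial | No diet change, no new supplement (8.4; Section 5, item 9); supplement with other forms of water (1.1b) | Partly. Drinking water is not named, and Section 1.1b is rationale text about the ELO arm |
| Patient already drinks it at Week 0 and continues | The same text | No. Continuing is neither a change nor new, and Section 3.4 is silent |
| Use is detected | Water diary and questions on changes in diet (Table 1, footnote a) | Possibly, but nothing prompts for it |

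**2. Volume open to substitution**

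Total 2-3 L/day minus 1.5 L of study water leaves 0.5-1.5 L/day. Only the top of that range, taken entirely as ELO water, equals the study dose.

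**3. The plan's own sample size**

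Inputs from Sections 11.1 and 11.2: d = 0.5, power 80%, two-sided 5%, 65 per arm. Allocation is 1:1 (Section 6.1).

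- Normal approximation: n = 2 × (1.960 + 0.842)² / 0.5² = 62.8, so 63 per arm.
- Two-sample t-test: 63.8, so 64 per arm.

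The stated 65 reproduces to within two patients. Power at 65 per arm with d = 0.5 is 80.8% (t-test), so there is little margin.

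**4. Illustrative dilution**

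Two quantities are assumptions, because the protocol gives neither: c, the share of controls who drink the product, and f, the fraction of the full effect that they obtain. The diluted effect is

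d_eff = 0.5 × (1 − c × f).

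Two cases bracket the advised extra volume:

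- f = 1: a fully effective amount.
- f = 0.5 / 1.5 = 1/3: 0.5 L/day, with effect proportional to dose.

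Power is for a two-sample t-test with 65 per arm, two-sided 5%.

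| c | d_eff, f = 1 | Power | d_eff, f = 1/3 | Power |
|---|---|---|---|---|
| 0% | 0.500 | 81% | 0.500 | 81% |
| 5% | 0.475 | 77% | 0.492 | 79% |
| 10% | 0.450 | 72% | 0.483 | 78% |
| 20% | 0.400 | 62% | 0.467 | 75% |

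Under f = 1, restoring 80% power would take 71, 79 or 100 per arm before dropout, against 64 with no dilution. These numbers show scale only; they are not a case for enlarging the trial.

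The model places use in controls only. Use in the ELO arm has a different effect that depends on the dose-response, and it is not modelled.

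**The case against.** The case against is substantial, and much of it stands.

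- **New use is already discouraged.** Starting an oxygenated water in the hope of better glucose control could be read as a diet change or a new health supplement. Section 1.1b's reference to other forms of water reads naturally as water other than ELO. This stands for new use, though a patient told to drink more water might see no breach. It does not reach existing users.
- **Blinding limits the motive.** Controls do not know that they are controls, and every patient already has 1.5 L/day delivered. Targeted crossover is less likely than in an open-label trial. This stands, but blinding does nothing about habitual use.
- **The visits might reveal it.** The diary and the questions on changes in diet are natural places for such use to surface. The diary template, the case record form and the consent pages are not available here, and any of them might ask about it or prohibit it. A reader might infer that use would certainly go unseen. The protocol does not support that; it shows only that no stated item asks specifically.
- **The size is hypothetical.** No rate is given, and the lower power figures assume a full-dose exposure. A reader might infer that the trial is underpowered, or that controls are free to drink any water, ELO included. Neither follows: the sample size reproduces on its own assumptions, and the fluid advice speaks of other water or beverages within a 2-3 litre total.
- **Defining a per-protocol deviation is commonly left to the SAP.** Agreed. What the protocol has to secure is that the information is collected.

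**Conclusion.** The gap is real but modest. The test product is on sale, self-chosen fluid is advised in both arms, and no passage explicitly excludes oxygen-enriched water, deals with existing users or specifically asks about use. The surrounding advice and the blinding reduce the risk of new use without closing it, and they leave existing users untouched.

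Use by controls would pull the result towards no difference. How far cannot be said from the protocol. If 5-20% of controls were exposed, power at 65 per arm would lie between 79% and 75% for 0.5 L/day with a proportional effect, and between 77% and 62% for a fully effective amount. Both ranges rest on an assumed rate, an assumed dose-response and use in controls only. They are illustrations, not forecasts.

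No figure or statement in the protocol is wrong on this point. It is a cheap improvement to trial conduct, worth making because the exposure cannot be reconstructed afterwards.

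**What to change.** - In Section 8.4, for both arms, state that fluids taken in addition to the study water should not be commercial ELO water or other oxygen-enriched water during the 24 weeks.
- At Week 0, ask about current use and have users stop before starting the study water.
- Add one line to the water diary and to the visit review to record any such use, so that it can be considered in the planned per-protocol analysis.

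The cost is one sentence, one question and one diary line. The study water, the visit schedule and the sample size do not change. There is one small downside: the instruction reminds patients that the product can be bought. Giving it in the same words to both arms, as a general rule about oxygen-enriched water, keeps it neutral with respect to allocation.

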### 8.5. Blinding

Both patients and attending staff reviewing the patients during the study will be blinded to the treatment arm and the type of water the patient is consuming.

The Sponsor will manufacture the 2 types of bottled water (ELO and control) at their factory. The water will be in similar unidentifiable bottles with labels specifying the Water Code allocated by CGH. The Sponsor will be aware of which Water Code is for ELO water and which water is for control water.The Sponsor will not have any access to information of water allocation to patients (because the delivery is managed by a third party commercial logistics vendor.

The logistics vendor will deliver the water to the patient’s home when activated by CGH using Water Codes to identify which water to deliver. (see attached plan in appendix 1)

The independent biostatistician will un-blind the treatment allocated to the patients only after the completion of the study and for analysis purpose.

### 8.6. Concomitant therapy

All medications taken by the patient during the study period will be documented.

# 9. SAFETY MEASUREMENTS

### 9.1. Safety Evaluation Criteria

Clinical observation and laboratory results will be used to evaluate the wellbeing of the patient on a continual basis throughout the duration of the study.

In the event that the Investigator considers that the wellbeing of an individual patient is unacceptably at risk as a result of participation in the study then the individual patient will be withdrawn from the trial.

In the event that the withdrawal of an individual also has wider implications for the wellbeing of other participating patients, then the study will be suspended and an investigation conducted to determine whether the trial should be continued in the proposed or a modified form or terminated.

### 9.2. Collecting, Recording and Reporting of Serious Adverse Events (SAEs)

A serious adverse event (SAE) is any untoward medical occurrence that:

- Results in death.
- Is life-threatening (immediate risk of death)
- Requires inpatient hospitalization or prolongation of existing hospitalization.
- Results in persistent or significant disability/incapacity.
- Results in congenital anomaly/birth defect.
- Is a Medically important event.

All SAE will be collected, documented, assessed and reported by the PI to SHS CIRB according to its guideline, and to the Sponsor in the prescribed SAE form.

There are no known adverse effects of drinking the ELO water.

Complaints will be recorded in the case notes, and possible adverse events will be recorded in a separate section in the case records form (see attached).

PI and co-investigators will determine the severity, causality and expectedness of adverse events. If the investigator determines that the event may jeopardize the subject and/or may require intervention to prevent one of the other adverse event outcomes, the important medical event will be reported as serious. Causality will be defined as related/not related, and expectedness will be based on reported adverse events in the summary of product of characteristics.

### 9.3. Safety Monitoring Plan

There is no Data Safety Monitoring Board for this study. The PI and coinvestigators will perform data and safety monitoring. The PI will regularly monitor the study to verify the authenticity, accuracy and completeness of data, that the safety and rights of subjects are protected and that the study is conducted in accordance with the latest approved protocol, GCP and all applicable regulatory requirements.

# 10. DATA ANALYSIS

### 10.1. Data Quality Assurance

Data integrity will be monitored to ensure the accuracy, completeness and legibility of data collected. The frequency of data monitoring will be determined by the recruitment rate.

### 10.2. Data Entry and Storage

Case record forms will be stored in locked cabinets in the research office. Research data will be stored in the designated computer which is password protected. Only the delegated study staff will have access to the research data. The study participants' identification will be coded and their records are only available to the investigators.

# 11. SAMPLE SIZE AND STATISTICAL METHODS

### 11.1. Determination of Sample Size

We expect there is a medium effect size ( ohen’s d = 0.5) between ELO water arm and control water arm. The minimum number subjects to be recruited into each arm will be 65 subjects (total 130 subjects) for the study to have 80% power with significance level of 5%. Taking into account a potential dropout rate of 15%, we aim to recruit 75 patients in each arm (total 150 subjects).

### 11.2. Statistical and Analytical Plans

Categorical data will be presented as frequency (percentage). Continuous data will be presented as mean (SD), unless specified otherwise. The differences in characteristics will be examined using Chi-Square test or Fisher’s Exact test for categorical variables, and 2-sample t-test or Mann Whitney U test for continuous variables. For repeated measures variables, mixed models analysis will be used to account for drop-outs.

A two tailed, p-value of <0.05 was considered statistically significant. Statistical analysis will be performed with SPSS statistical software, version 19.0 (IBM Corp. Armonk, NY).

A statistical analysis for month 3 data is planned in order to study the short term outcomes.

This RCT will be analysed by both intention-to-treat (ITT) and per protocol (PP) approach. Patients’ non-compliance will be monitored via their water diary. The compliance rate will then be adjusted in the data analysis.

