###### Table 1: Trial schedule

| **Week** | **0** | **6** (+/– 1 week) | **12**  (+/– 1 week) | **24**  (+/– 1 week) |
| --- | --- | --- | --- | --- |
| Consent taking | **X** |  |  |  |
| Inclusion &  Exclusion Criteria  Check | **X** |  |  |  |
| CGH clinic review^a^ | **X** | **X** | **X** | **X** |
| Vital Signs (BP) | **X** | **X** | **X** | **X** |
| Height and Weight | **X** | **X** | **X** | **X** |
| Blood and Urine tests^b^ | **X** | **X** | **X** | **X** |
| Completion of study |  |  |  | **X** |

*a :CGH review will be performed on Week 0, 6, 12, 24 and whenever there is any adverse events. Review will include review of water diary and to ask patient whether there has been any adverse effect, and / or changes in medications, diet and physical activities*

*b: Blood and Urine tests for HbA1c, Haemoglobin, Liver function test (ALT, AST, GGT), Serum creatinine and calculated eGFR, Fasting Lipid profile – Triglyceride, Total Cholesterol, LDL, HDL, Fasting plasma glucose, Plasma Hypoxia inducible factor HIF-1α, Long chain acyl carnitine (C16) and Urine ACR*

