### 6.1. Randomisation and Blinding

Randomization:

Stratified randomization will be performed for this study. Recruited patients will be stratified according to their gender and will be randomly assigned to ELO water arm or Placebo drinking water arm in a 1:1 ratio. A randomisation list will be generated by an independent biostatistician. Blinding of drinking water bottles will then be packaged according to the randomization list. Treatment allocation will be performed by the study nurse once all the recruitment criteria have been fulfilled and consent obtained.

Blinding:

ELO water Pte Ltd (A Hyflux Group Company) will blind the Hyflux factory bottled ELO water and Hyflux factory bottled Placebo drinking water by similar packing and label it as Water A or Water B, to unidentified drinking water bottles for both arms of the study. Water A or Water B for ELO water or Placebo drinking water will be pre-determined by the independent biostatistician.

Water bottles will be delivered to the patient’s home at regular intervals by an independent logistics team (who will not know what is Water A and Water B). A designated CGH staff member will co-ordinate with the logistics team for delivery of the correct type of bottled water to the patients. PI, attending investigators, study team members, and patients will not be able to identify the type of water the patient has been consuming.

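### Section 11.2 names no use of baseline HbA1c or the gender stratum in the analysis; stating both is a free gain in precision

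*Protocol*

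**What the plan says.** Section 11.2 gives the analysis in a few sentences. Differences in characteristics are to be examined, for continuous data, by "2-sample t-test or Mann Whitney U test for continuous variables". Variables measured repeatedly are to go into a mixed model, for which no fixed effects are listed and none excluded. The section also says that the compliance rate from the water diary will be adjusted for; no other adjustment variable is named. On the significance level: "A two tailed, p-value of <0.05 was considered statistically significant".

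Two pre-randomisation variables are available for every patient:

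- **Gender.** Section 6.1: "Recruited patients will be stratified according to their gender and will be randomly assigned to ELO water arm or Placebo drinking water arm" (1:1). Section 5 says the same.
- **Baseline HbA1c.** Footnote b of Table 1 lists "Blood and Urine tests for HbA1c, Haemoglobin, Liver function test" and further tests, and the table schedules them at weeks 0, 6, 12 and 24. The entry range in Section 3.3 is 8.0% to 11%, on a value from the last 6 months. HbA1c is not a stratification factor.

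Section 11.1 bases the sample size on a standardised difference: "We expect there is a medium effect size" (d = 0.5). It asks for 65 per arm for 80% power at the 5% level, and 75 per arm after allowing for 15% dropout. It does not say whether d refers to the week-24 value or to the change from baseline.

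**The concern.** HbA1c at entry usually predicts HbA1c later, so a comparison that ignores it leaves explainable variation in the error term. If the arms differ by chance at baseline, a comparison of final values carries part of that difference into the estimate for this trial, and stratifying by gender does not protect against it. An analysis that omits the stratification factor also tends to give slightly conservative standard errors.

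Section 11.2 does take up adjustment, but the one variable it names is measured after randomisation. The two variables fixed before randomisation, which are the natural choices, are not mentioned. Section 11.2 also does not say which of its methods carries the primary HbA1c comparison. Covariates chosen after unblinding would be open to challenge. What is at stake is the width of the confidence interval and the clarity of the primary analysis, not its validity.

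**Working it through.** **Inputs from the protocol:** d = 0.5, two-sided 5%, 80% power, 65 per arm, 75 after 15% dropout (Sections 11.1 and 11.2); 1:1 allocation (Section 6.1).

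**Assumed, because the documents do not give them:** the correlation ρ between baseline and week-24 HbA1c (0.3 to 0.7); equal SDs at the two times; the share of HbA1c variance explained by gender (R² 1–5%).

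**1. Reproduce the plan's figure.**
- n per arm = 2(1.96 + 0.8416)² / 0.5² = 62.8, so 63. The t-distribution solution is 63.8, so 64. The plan's 65 is consistent with an unadjusted two-sample comparison.
- Power at 65 = Φ(0.5·√(65/2) − 1.96) = Φ(0.890) = 81.3% (80.8% by the t-distribution).
- After 15% loss from 75 per arm, 63.75 remain, with power 80.6% (80.0% by t).

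**2. Error variance under each analysis,** with the variance of a single HbA1c value set to 1:
- week-24 value, unadjusted: 1
- change from baseline, unadjusted: 2(1 − ρ)
- adjusted for baseline: 1 − ρ²

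So adjustment multiplies the variance by 1 − ρ² relative to the week-24 value, and by (1 − ρ²)/[2(1 − ρ)] = (1 + ρ)/2 relative to change.

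**3. Power after adjustment** = Φ((0.5/√ratio)·√(65/2) − 1.96). At ρ = 0.5 both ratios are 0.75: 0.5/√0.75 = 0.577, 0.577 × 5.70 = 3.29, and Φ(3.29 − 1.96) = 90.8%.

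| Assumed ρ | d on week-24 value, adjusted: n per arm for 80% / power at 65 | d on change, adjusted: n per arm for 80% / power at 65 | d on week-24 value, analysed as simple change: power at 65 |
|---|---|---|---|
| 0.3 | 58 / 84.8% | 41 / 94.2% | 67.3% |
| 0.4 | 53 / 87.5% | 44 / 92.6% | 74.0% |
| 0.5 | 48 / 90.8% | 48 / 90.8% | 81.3% |
| 0.6 | 41 / 94.6% | 51 / 89.0% | 89.0% |
| 0.7 | 33 / 97.9% | 54 / 87.1% | 95.7% |

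The unadjusted reference for the second and third columns is 63 per arm and 81.3%. Adjustment gains at every ρ shown, on either scale.

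**4. Gender alone.** With ratio 1 − R², power at 65 is 81.7% at R² = 1% and 83.3% at R² = 5%, a gain of at most 83.3 − 81.3 = 2.0 points.

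**5. If week 0 is itself a modelled outcome.** A model with a common baseline mean for both arms behaves much like baseline adjustment, so little is left to gain. A model with free arm-by-time terms gives a change-type contrast, and the gain is then the distance from that contrast to the adjusted one. With d on the week-24 value, this is the second column minus the last: 97.9 − 95.7 = 2.2 points at ρ = 0.7 and 90.8 − 81.3 = 9.5 points at ρ = 0.5. It is larger at lower ρ.

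**The case against.** The case on the other side is substantial, and most of it stands.

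- **Silence is not exclusion.** A reader might infer that the protocol plans a mixed model without covariates. It does not say so: Section 11.2 gives no model terms, and a statistical analysis plan that is not shown may supply them.
- **The two-sample tests are not assigned to HbA1c.** That sentence concerns differences in characteristics. HbA1c is measured four times and falls more naturally under the mixed model. A reader might infer that the primary endpoint will be tested by an unadjusted t-test; the text does not establish this.
- **Baseline may already be used.** Week 0 is one of the scheduled measurements. If it is modelled, it is too strong to say that baseline imbalance passes straight into the estimate; that describes only a comparison of final values.
- **A test averaged over visits is only a possibility.** It would arise if the arm-by-visit term were left out, and nothing says that it will be.
- **The power figures have limits.** They compare adjustment with an unadjusted single-visit test, rest on an assumed ρ, and need a continuous endpoint. Section 2.4 words the primary endpoint as reaching a reduction of at least 0.5%; if that means a responder outcome, these figures do not apply. The restricted entry range may also lower ρ, so the lower end of the table matters.
- **Gender contributes little,** and the trial meets its power target without any adjustment.

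What the objection does not remove is that Section 11.2 names an adjustment variable and passes over the two pre-randomisation ones that the design supplies. Even on the favourable reading, the primary model is not identified. Whether adjusting for compliance is sound is a separate question and is not relied on here.

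**Conclusion.** The point holds as a free improvement, not as the correction of an error. Section 11.2 states no use of baseline HbA1c or of the gender stratum. Following it as written risks a loss of precision; omitting these covariates does not bias the comparison, and it does not undermine the sample size, which reproduces.

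The size depends on a correlation that the documents do not give. Over the assumed range 0.3 to 0.7, power at 65 per arm moves from about 81% to between 85% and 98% (d on the week-24 value) or between 94% and 87% (d on change), measured against an unadjusted single-visit comparison of a continuous HbA1c outcome. It may be close to nil if the mixed model already includes week 0 with a common baseline mean. Nearly all of the gain comes from baseline HbA1c; gender belongs in the model mainly so that the analysis matches the stratified randomisation.

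**What to change.** State in Section 11.2, before any unblinded analysis:

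- The primary analysis of HbA1c is a mixed model for weeks 6, 12 and 24 with arm, visit, arm-by-visit, baseline (week 0) HbA1c, baseline-by-visit and gender.
- The primary estimate is the arm difference at week 24. The planned month-3 analysis can take the week-12 contrast from the same model.
- Other continuous endpoints are adjusted for their own baseline value and gender.
- The two-sample tests, if kept, are limited to the description of characteristics.

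If a statistical analysis plan already specifies this, Section 11.2 need only be brought into line with it. The cost is analysis wording: no new data, visits or patients, and the planned 75 per arm can stay.
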